### **Lay Summary**

Preventive screening for abdominal aortic aneurysm (AAA) in men aged 65–74 years using ultrasound scanning has proven to be a simple and safe method to prevent rupture.

Approximately 4% of men have such an asymptomatic dilation. The vast majority of aneurysms (80–85%) diagnosed through screening are too small to pose an immediate risk; however, up to half of these may grow to a dangerously large size requiring surgical intervention to prevent rupture. Preventive surgery carries a mortality risk of approximately 3%, compared with around 90% in the event of rupture.

There is increasing evidence that aneurysm growth can be slowed through smoking cessation, low-dose aspirin, cholesterol-lowering medication, and antihypertensive treatment—preventive measures that simultaneously reduce the increased cardiovascular risk faced by these patients.

Furthermore, such preventive screening can likely be combined advantageously with other preventive examinations.

Approximately 5–10% of men over the age of 60 show signs of early peripheral arterial disease (PAD) in the lower limbs. This condition is often benign with respect to limb outcomes—although a proportion ultimately require amputation—but more importantly, it is a strong risk marker for thrombotic events elsewhere in the body. Approximately 25–30% of these individuals will die from cardiovascular disease within five years, and an even larger proportion will be hospitalized due to cardiovascular disease. Cholesterol-lowering interventions, smoking cessation, low-dose acetylsalicylic acid, increased physical activity, healthy dietary habits, and blood pressure control reduce this excess risk of cardiovascular disease and mortality by at least 20–30%.

Early PAD can be diagnosed reliably and without adverse effects by measuring ankle blood pressure and comparing it with arm blood pressure. This can be done quickly, reliably, and non-invasively using a portable Doppler ultrasound device and blood pressure cuff, making it suitable for screening purposes.

There are thus well-documented public health benefits to be gained from screening for and preventing vascular diseases—both in terms of avoided premature deaths and reduced hospital admissions and amputations. There will also be indirect positive effects for hospitals through reduced pressure on surgical and intensive care capacity in vascular surgery departments, cardiology departments, and neurological departments.

It therefore appears highly relevant to offer combined screening for abdominal aortic aneurysm, peripheral arterial disease, and hypertension, although the benefits and costs of such a program have not yet been fully evaluated.

The primary objective of the study is therefore to assess the benefit and cost-effectiveness of a combined cardiovascular screening program for men aged 65–74 years through a randomized,

clinically controlled trial (lottery-based trial), in which half of 40,000 men aged 65–74 years are invited to preventive screening at regional hospitals, while the other half serve as a control group.

The principal investigator will train six nurses in screening methods, information requirements, and blood sampling. These nurses will bring mobile equipment to regional hospitals, where examinations will be conducted along with follow-up for positive findings.

The project secretary will continuously invite men for screening at their "regional" hospital with 2–4 weeks' notice. A brief lifestyle and health questionnaire will be enclosed, along with the option to decline participation in writing or request an alternative appointment. Participants will receive initial oral information, including the option of a reflection period of a few weeks; if this is waived, written informed consent will be obtained before the examinations are conducted.

Men with positive findings will be offered a follow-up informational consultation within one week, during which findings are explained and the aforementioned preventive measures initiated. In addition to lifestyle counseling, it will often be necessary to initiate treatment with low-dose aspirin and cholesterol-lowering medication. This medication carries a small risk of gastric irritation or bleeding, as well as muscle pain. These adverse effects occur in only a few per thousand individuals and must be weighed against the expected benefit. During this consultation, consent will also be obtained for blood sampling for a biobank for prognostic studies, conducted in connection with cholesterol testing. Finally, annual follow-up will be offered.

The participants are mature men capable of making fully independent decisions regarding participation, and emphasis is placed on providing as comprehensive an explanation as possible in the invitation, which is sent 2–4 weeks prior to the scheduled examination. After oral information, time for consideration will be provided. In the event of a positive finding, an in-depth outpatient consultation will be offered within one week. Thus, opportunities for reflection are provided at multiple stages, and participants are explicitly encouraged to bring a companion if they wish.

Offering screening for AAA is known to reduce quality of life in the period prior to examination, but this normalizes immediately afterwards—except in cases of positive findings. It is unclear whether this is due to the diagnosis itself or comorbidity, but the reduction is modest. This is likely also the case for PAD. This "side effect" must be weighed against the substantial preventive benefit achieved.

More problematic in AAA screening is the risk of death due to rupture in conservatively treated cases, as well as perioperative deaths among operated patients whose aneurysms might never have ruptured. There is an immediate operative mortality risk of approximately 3%, which must be weighed against a rupture-related mortality risk of around 90%. This ethical dilemma is serious but currently unavoidable. Exploration of the planned biobank aims, among other objectives, to develop prognostic models. Participation in the biobank exposes participants to a very small risk of infection or phlebitis associated with blood sampling, which is in any case necessary for cholesterol determination.

Effectiveness and cost analyses will be conducted using registry-based methods and will therefore not impose any burden on participants.

The project is supported by the EU's Seventh Framework Programme. No remuneration is provided to participants.

The biobank will be maintained for 10 years, after which the samples will be anonymised.

## Background

Screening for abdominal aortic aneurysm (AAA) in men aged 65–74 years has been shown to reduce AAA-related mortality. Research from Regionshospitalet Viborg, published in the *British Medical Journal* in March 2005, demonstrated that it is sufficient to screen 352 Danish men over the age of 65 for AAA to prevent one death due to AAA rupture within the subsequent five years (1). The benefit has also been shown to be reasonably proportionate to the costs in randomized studies (2–4). However, there are currently no recommendations for AAA screening in Scandinavia, although a Danish health technology assessment may be forthcoming.

The vast majority of AAAs diagnosed through screening are too small to pose an immediate risk, but up to half of them expand to sizes requiring surgical intervention. Increasing evidence suggests that aneurysm growth can be slowed through smoking cessation (5;6), low-dose aspirin (7;8), statin therapy (9), and ACE inhibitor treatment (10)—preventive measures that simultaneously reduce the increased cardiovascular risk faced by these patients (11). The aforementioned screening studies did not implement such preventive measures; consequently, the benefit and thus the cost-effectiveness may potentially be even greater.

In addition, invitations to AAA screening could advantageously be combined with further preventive examinations. International scientific studies indicate that approximately 5–10% of men over the age of 60 show signs of peripheral arterial disease (PAD) in the lower extremities, with prevalence increasing with age (12–14). Of these individuals, approximately 25–30% will die from cardiovascular disease within a five-year period, and an even larger proportion will be hospitalized due to cardiovascular disease (14–16). Cholesterol-lowering interventions, smoking cessation, low-dose acetylsalicylic acid, increased physical activity, healthy dietary habits, and blood pressure control reduce this excess risk of cardiovascular disease and death by at least 20–25% (14;17–19).

PAD can be diagnosed quickly, reliably, and non-invasively using a portable Doppler ultrasound device and a blood pressure cuff. PAD is defined as an ankle–brachial systolic blood pressure index (ABI) of <90% (14).

There are therefore well-documented health benefits to be gained from screening for and preventing vascular diseases, both in terms of avoided premature deaths and avoided hospital admissions and amputations. There will also be a secondary positive effect for hospitals through reduced pressure on surgical capacity and intensive care capacity in vascular surgical departments.

It therefore appears highly relevant to offer combined screening for AAA, PAD, and hypertension, although the benefits and costs of such a program have not yet been fully elucidated.

## Purpose:

1. The primary objective of the study is to assess the effectiveness and cost-effectiveness of a combined cardiovascular screening program for men aged 65–74 through a randomized, clinically controlled trial.

2. Secondary objectives include:

a. A prevalence study of abdominal aortic aneurysm (AAA), peripheral arterial disease (PAD), and previously undiagnosed hypertension among men aged 65–74. This will be a cross-sectional study conducted in connection with the screening offer, as well as a comparison with the corresponding AAA prevalence identified in the screening study conducted in Viborg County during 1994–1998,

as both the frequency of planned operations and emergency operations for AAA has increased over the past decade, possibly indicating a rising prevalence.

b. An evaluation of the effect of smoking cessation campaigns and treatment with aspirin and statins on AAA growth rate, need for surgery, and cardiovascular mortality. This will be achieved by comparison with the AAA cohort diagnosed through screening in the period 1994–1998, which was not offered any form of preventive intervention.

c. A contemporary prognostic study of patients with PAD who are offered relevant preventive measures.

d. Predictor studies. Previous studies have identified several moderate serological predictors of the clinical course of non-surgically treated AAAs. These will be combined in regression models and validated. For this purpose, a biobank will be established with blood samples collected at the time of diagnosis and at the first follow-up. A corresponding biobank will be established for PAD.

e. Assessment of the psychological consequences of cardiovascular screening, evaluated using the SF-12 questionnaire (20).

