#### **Target population (men aged 65–74 years)**

In order to maximize the potential to demonstrate an effect, men aged 65–74 years are screened due to the high prevalence of disease and a long expected remaining life expectancy. Screening men older than 74 years would likely yield a high prevalence of AAA and PAD; however, mortality from other diseases is high and the acceptance rate is low. Screening men younger than 65 years would result in lower mortality, but also lower prevalence and a lower rupture rate.

The prevalence of PAD and AAA is lower in women and occurs later in life; therefore, offering screening to women is expected to result in lower participation and higher mortality from other causes, and consequently a lower overall effect.

As of 1 January 2008, there will be approximately 40,000 men aged 65–74 years in the Central Denmark Region.

These men constitute the target population for the study, with no exclusion criteria.

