### **Power calculations**

With a 75% attendance rate and a PAD prevalence of 8%, assuming a five-year total mortality of 28% compared with 15% in the control group, a relative risk (RR) of 0.93 is calculated. With a 5% significance level and a sample size of  $2 \times 20,000$ , the statistical power is estimated at 85%.

With a 75% attendance rate and 8% PAD prevalence, where 70% experience a cardiovascular-related hospital admission within five years compared with 45% in the control group, an RR of 0.93 is calculated. With a 5% significance level and a sample size of  $2 \times 20,000$ , the statistical power is estimated at 99%.

The expected absolute reduction in mortality is based on survival data from the screening study of 65–73-year-old men in Viborg County, as follows: an expected 10-year mortality of 36% in the control group, corresponding to 7,200 deaths. If the relative mortality with a screening victim is 0.93, as calculated, this corresponds to 6,696 deaths. This represents a difference of 504 prevented deaths, corresponding to an absolute mortality risk reduction of 2.5%.

The power calculations are conservative, as they are based solely on the expected benefit of PAD screening. A recent meta-analysis of the four existing randomized trials showed that screening for AAA results in a significant absolute mortality reduction of 3%. However, these studies did not offer general cardiovascular prevention to screening-positive individuals. One third of men with screen-detected AAA also have signs of PAD. A cautious estimate of the potential combined benefit would therefore be an absolute mortality risk reduction of at least 4–5%.

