### **Expected number of examinations, operations, and follow-up visits**

Three screening teams will be established—one covering the former Aarhus County, and one each corresponding to the former Viborg and Ringkøbing Counties. At each site, 34 men are invited daily at 10-minute intervals (with an expected primary participation rate of 70%). Non-responders are invited at five-minute intervals. In this way, the target population is expected to be examined within 1.5 years.

Examinations take place four days per week from 9:00 to 12:00 and from 12:30 to 15:00. The nurses' positions will therefore correspond to 30 hours per week, including transport time. From Monday to Thursday, approximately 150 examinations are performed, with an expected finding of approximately 4 AAA cases and 8 PAD cases per site.

Patients attend outpatient consultations on the fifth day of the week in the same room from 9:00.

Thirty minutes are allocated per patient. Every tenth AAA case is expected to be referred for surgical evaluation, of which 90% are expected to undergo surgery. This corresponds to 1–2 additional AAA operations per month per department.

The departments' consultant vascular surgeons foresee no operative or nursing-related capacity problems, primarily because emergency operations require several times longer operative and hospitalization times—especially in intensive care units—compared with elective procedures.

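### Objective 2b claims a prevention effect on AAA growth, surgery and cardiovascular death from a 1994–1998 historical cohort, so treatment cannot be separated from calendar period

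*Protocol*

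**What the plan says.** The protocol's Purpose section words objective 2b as "An evaluation of the effect of smoking cessation campaigns and treatment with aspirin and statins on AAA growth rate, need for surgery, and cardiovascular mortality". It then fixes the method: a "comparison with the AAA cohort diagnosed through screening in the period 1994–1998, which was not offered any form of preventive intervention". Objective 2a uses the same earlier study for prevalence, as "a comparison with the corresponding AAA prevalence identified in the screening study conducted in Viborg County during 1994–1998", and gives as its reason that both planned and emergency AAA operations have become more frequent over the past decade.

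The Power calculations section describes the earlier work as a "screening study of 65–73-year-old men in Viborg County". The new population is wider: "As of 1 January 2008, there will be approximately 40,000 men aged 65–74 years in the Central Denmark Region". The section on expected numbers of examinations lists three screening teams, "one covering the former Aarhus County, and one each corresponding to the former Viborg and Ringkøbing Counties", so the old study area lies inside the new one.

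Under Follow-up consultation, preventive advice and treatment are offered to AAA cases as a group. Under Randomization, the control group is not screened. Outcome measures and statistical analyses describes Cox regression between the two randomised groups and gives no method for the historical comparison.

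**The concern.** Objective 2b is worded as a causal question and answered with a non-randomised control group from a decade or more earlier. Randomisation gives no help, because AAAs in the control arm are not looked for and so form no concurrent untreated group. Anything that changed between the two periods and bears on growth, surgery or cardiovascular death would be read as the result of prevention.

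Two objectives in the same section also pull against each other. Objective 2a looks for change over time between the two cohorts. Objective 2b can claim an effect only if, prevention apart, nothing relevant changed. The change that 2a reports, in operation frequency, bears directly on one of the 2b endpoints. At stake is whether a stated secondary objective can support the conclusion it announces.

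**Working it through.** The protocol gives no sample size, effect size or trend for 2b, so there is no stated figure to reproduce. The check sets the two cohorts side by side and then illustrates how large a period effect could be.

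**1. The two cohorts**

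| | Historical cohort | New cohort | Source in protocol |
|---|---|---|---|
| Period | 1994–1998 | late 2008 to early 2010 | Purpose; Five-year budget (3 + 12 + 3 months) |
| Area | Viborg County | Former Aarhus, Viborg and Ringkøbing Counties | Purpose; Expected number of examinations |
| Age | 65–73 | 65–74 | Power calculations; Target population |
| Prevention offered | None | All AAA cases | Purpose; Follow-up consultation |

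Prevention offered takes one value in each period. A model with terms for both period and prevention therefore cannot estimate them separately, whatever other covariates it holds.

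**2. Time between cohorts.** The midpoints are 1996 and 2009, so the gap is 2009 − 1996 = 13 years.

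**3. Illustrative size of a period effect.** The annual decline *r* is an assumption. Relative fall over 13 years = 1 − (1 − *r*)^13.
- *r* = 1%: 1 − 0.99^13 = 12%
- *r* = 2%: 1 − 0.98^13 = 23%
- *r* = 4%: 1 − 0.96^13 = 41%

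**4. Chance of a false finding, also illustrative.** New AAA cases: 20,000 invited × 75% attendance × 4% prevalence = 600. The weekly figures under Expected number of examinations (4 per 150) give 20,000 × 0.75 × 4/150 = 400. Assumed, because the protocol does not give them: 100–400 historical cases with a five-year cardiovascular mortality of 15–25%. With no true prevention effect, the chance that a two-sided 5% test of two proportions shows a significant benefit is Φ[(d − 1.96·se₀)/se₁]. Here d is the difference due to period alone, se₀ the pooled standard error and se₁ the unpooled one. With 600 new cases:

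| Assumed fall between eras | Chance of a false benefit |
|---|---|
| 0% | 2.5% |
| 10% | 7–15% |
| 20% | 15–47% |
| 30% | 28–82% |

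Each range runs from 100 historical cases at 15% mortality to 400 at 25%.

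**5. Direction by endpoint.** Steps 3 and 4 concern cardiovascular mortality, where a falling background rate would favour the new cohort. For need for surgery, the only trend the protocol reports is upward. If it reflects readier operating, it would count against prevention. For growth rate, the protocol gives nothing from which to sign or size a bias.

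**6. Age and area.** With equal numbers at each year of age, the mean is 69.0 for 65–73 and 69.5 for 65–74, a gap of 0.5 year. The area difference can be removed by looking at the former Viborg County alone.

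**The case against.** The strongest reply is that 2b is a brief secondary objective that names a comparator, with the method left to an analysis plan that is not shown. A reader might infer that the comparison will be crude. The protocol does not say so: it is silent on adjustment, and restriction or covariate adjustment may be specified elsewhere. That part of the reply stands. It does not rescue the causal wording, because the protocol itself fixes both the claim and the comparator, and no later adjustment separates prevention from period.

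A reader might also set the illustrated 12–41% against the 20–25% in the Background section and conclude that secular change would swamp the expected benefit. The documents do not support that. The 20–25% is a minimum reduction in the excess risk of people with PAD, not an expected change in cardiovascular mortality among AAA patients, and the annual decline is an assumption.

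Nor can one say that any change in operating practice would be credited to the programme. The reported rise in operations could work against it.

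Age and area are minor: half a year in mean age, and an old study area that lies within the new one. No passage shows that AAA prevalence differs between the counties. Objective 2a makes no treatment claim, and change over time is its subject, so only the age and area mismatch applies to it.

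Finally, a concurrent untreated AAA group is not available in this design. That is true, and it is a reason to state the limitation rather than to drop the comparison.

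**Conclusion.** The point holds for objective 2b. Its wording promises an effect that its design cannot identify, because offered prevention and calendar period are the same variable in these data. This rests on the protocol's text alone and needs no assumption.

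The size of the resulting bias is not known. The 12–41% range depends on an assumed decline of 1–4% a year, and the false-benefit chances depend further on an assumed historical cohort size and mortality. They show only that a modest trend could matter. The direction may differ by endpoint.

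The age and area mismatch is real, small and avoidable, and it is the only part that carries over to 2a. The randomised comparison of the primary outcomes does not depend on any of this. The change is worth making because it is cheap and alters what the trial can conclude from 2b.

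**What to change.** - Reword 2b as an association between two screening eras, one with and one without an offer of prevention. Name calendar period as confounding that the analysis cannot remove, with its possible direction for each endpoint.
- Limit both historical comparisons to men aged 65–73, and age-standardise the prevalence comparison in 2a.
- For 2b, adjust for baseline aortic diameter and age, and for smoking if the historical cohort recorded it. The new cohort has all three: diameter is measured at screening, and smoking is asked in the Appendix 2 questionnaire.
- Report the former Viborg County subset alongside the whole-region result, using the address and site data already held. Making the subset the sole main analysis would give up many of the new cases to cure a minor mismatch.

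The cost is wording and analysis only, with no new data collection in the new cohort. The downside is a weaker claim for 2b and less precision in the matched subset.

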#### **Target population (men aged 65–74 years)**

In order to maximize the potential to demonstrate an effect, men aged 65–74 years are screened due to the high prevalence of disease and a long expected remaining life expectancy. Screening men older than 74 years would likely yield a high prevalence of AAA and PAD; however, mortality from other diseases is high and the acceptance rate is low. Screening men younger than 65 years would result in lower mortality, but also lower prevalence and a lower rupture rate.

The prevalence of PAD and AAA is lower in women and occurs later in life; therefore, offering screening to women is expected to result in lower participation and higher mortality from other causes, and consequently a lower overall effect.

As of 1 January 2008, there will be approximately 40,000 men aged 65–74 years in the Central Denmark Region.

These men constitute the target population for the study, with no exclusion criteria.

